#### Health practitioner education

2.4.3

Simultaneously with the peer‐group education, participants in IG2 (*N* = 30) will be educated by a health practitioner in six‐60‐min sessions for 3 weeks (twice a week). The content and delivery route of each session will be similar in two intervention groups.

#### Comparison group

2.4.4

The CG (*N* = 30), as well as IGs, will receive school routine education provided by school counsellors. In the Iranian educational system, in each school, a counsellor position has been defined that she usually answers students' questions in many different areas as well as menstrual concerns.

### Sample size

2.5

Sample size will be determined at CI: 95% and Power: 80%, Large Cohen effect size = 0.8, in the intervention group, compared to the control group, and by the assistance of following formula:
$$n=\frac{2*{\left(z1‐\frac{\alpha }{2}+z1‐\beta \right)}^{2}}{E{\text{.S}}^{2}}=\frac{2*{\left(1.96+0.84\right)}^{2}}{{\left(0.8\right)}^{2}}=25.$$
z0.975=1.96z0.8=0.84.

By considering an attrition rate 25%, the sample size in each group will be calculated, 30 students.

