**Methods:**

Ninety 11th‐grade students with moderate to severe PMS will be allocated to Intervention Group 1 (IG1), Intervention Group 2 (IG2) and Comparison Group (CG). Three weeks (six online sessions) of parallel education will be implemented in IG1 by trained peer educators and in IG2 by a health practitioner. The primary outcome will be changes in PMS severity score between three groups over time (measured by Daily Record of Severity of Problems). Secondary outcomes include changes in Premenstrual Dysphoric Disorder and General Health. Data collection will be conducted in two‐time points, at baseline, and at the end of the intervention.

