### Recruitment and randomization

2.6

Three high population public secondary high schools in both districts in Sari city will be selected purposefully. In each school, all 11th‐grade students will fill out the socio‐demographic menstrual characteristics checklist, GHQ‐28 Items, and PSST which is a retrospective questionnaire to screen eligible participants. After that, schools will be randomly allocated to one of three study arms: (a) Peer‐group education (IG1); (b) Health practitioner education (IG2); (c) Comparison Group (CG) by using a random number table. Following recruitment and verification of study eligibility, required sample size (30 students in each group) will be selected randomly by a random allocation sequence generating using the built‐in random number generator in Microsoft Excel (Cheusheva, 2020). They will complete the DRSP (during two consecutive menstrual cycles). Before random sampling, ten volunteer students will be selected as peer educators purposefully and will be trained by the PI. At the end of the final session, the PI will select six students as peer educators by assistance of school staff. Since the intervention is educational, it will not be possible to design a blind study. The students who meet the inclusion criteria will be informed completely about the protocol of the study.

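### Thirty students per arm does not cover 25% attrition from 25 evaluable; at that loss the trial misses its stated 80% power

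*Protocol article*

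**What the plan says.** Section 2.5 (Sample size) of the protocol article sets the error rates: "Sample size will be determined at CI: 95% and Power: 80"%. It takes a "Large Cohen effect size = 0.8, in the intervention group, compared to the control group". It prints the usual two-group formula with normal quantiles 1.96 and 0.84 and reports 25 per group.

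It then moves from evaluable to enrolled numbers in one sentence: "By considering an attrition rate 25%, the sample size in each group will be calculated, 30 students".

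Thirty per arm is the working figure elsewhere. Section 2.6 (Recruitment and randomization) says the "required sample size (30 students in each group) will be selected randomly". Sections 2.4.2, 2.4.3 and 2.4.4 give 30 for each of the three groups, and the abstract gives a total of ninety. The article describes no over-recruitment and no replacement of students who drop out.

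**The concern.** A sample size statement ties together an effect, a power, an attrition rate and an enrolled number. Here the enrolled number does not follow from the other three. If a quarter of the students are lost, as the article allows for, fewer than the required 25 per arm provide outcome data, and the comparison has less power than the article claims.

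The loss is plausible. The primary outcome at T1 needs daily symptom records over two menstrual cycles (section 2.9.3), and several exclusion criteria continue to apply during the study (section 2.3).

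What is at stake is how the result will be read. A non-significant difference would be judged against 80% power that the stated attrition does not leave. The assumed effect is already a large one, so there is little reserve: for any smaller true effect the power is lower still.

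**Working it through.** **Inputs, all from section 2.5:** two-sided α = 0.05 (z = 1.96); power 80% (z = 0.84); standardised effect d = 0.8; attrition 25%; stated enrolment 30 per group.

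**Step 1. Reproduce the evaluable number.**

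n = 2(1.96 + 0.84)² / 0.8² = 2 × 7.84 / 0.64 = 24.5, rounded up to 25. This agrees with the article.

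**Step 2. Allow for attrition.** To keep n students after losing a fraction a, enrol n/(1 − a).

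| Route | Result | Rounded up |
|---|---|---|
| 25 / 0.75 | 33.3 | 34 |
| 24.5 / 0.75 (unrounded start) | 32.7 | 33 |
| 25 × 1.25 (invalid shortcut) | 31.25 | 32 |
| 24.5 × 1.25 (invalid shortcut) | 30.6 | 31 |

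None gives 30. The figure equals 25 × 1.20, a 20% add-on. It also equals 24 × 1.25, but that starts from a number below the formula's 24.5 and below the 25 that the article prints.

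**Step 3. What attrition does 30 tolerate?** 1 − 25/30 = 5/30 = 16.7%.

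**Step 4. What remains at 25%?** 30 × 0.75 = 22.5, so 22 or 23 students per arm.

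**Step 5. Power at d = 0.8, two-sided 5%.** The normal approximation is Φ(d√(n/2) − 1.96). For n = 22: 0.8 × √11 − 1.96 = 0.693, and Φ(0.693) = 0.756. The t-test values come from the noncentral t distribution.

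| Evaluable per arm | Normal approximation | t test |
|---|---|---|
| 22 | 75.6% | 73.6% |
| 22.5 | 76.5% | 74.6% |
| 23 | 77.4% | 75.6% |
| 25 | 80.7% | 79.2% |
| 25.5 (34 enrolled, 25% lost) | 81.5% | 80.0% |

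**Step 6. Effect detectable with 80% power.** 2.8 × √(2/n) gives 0.844 at n = 22, 0.835 at n = 22.5 and 0.826 at n = 23, against the planned 0.80.

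**The case against.** The arithmetic slip is hard to defend, but three points can be made about its weight.

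- **It is small.** By the protocol's own normal approximation, power at 22.5 per arm is 76.5%, about 3.5 points below 80%. The detectable effect moves by about 0.03 to 0.04 SD, and the 0.8 is a conventional large effect with no pilot data or minimal important difference cited for it. The slip biases no estimate. This stands as a description of size. It does not make the sentence correct.
- **The planned analysis may be more efficient.** Section 2.10 plans an ANCOVA adjusted for baseline, while the formula is for an unadjusted comparison. With a baseline-to-final correlation r, the residual variance is multiplied by about 1 − r². Twenty-two per arm would be as informative as 25 if r² = 1 − 22/25 = 0.12, so r of about 0.35. That is possible, but the article gives no correlation and takes no credit for one. At r = 0 nothing is recovered. The printed calculation has to hold on its printed inputs.
- **Intention-to-treat analysis is planned** (section 2.10). That decides which group a student is analysed in; it does not by itself supply a missing outcome.

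Nor can a fuller protocol or analysis plan explain this away as condensation. The article prints the inputs, the formula and the result, and the result does not follow.

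**Conclusion.** The concern holds. The 25 evaluable students per group reproduce exactly; the 30 enrolled do not. At the stated attrition the number needed is 34 (33 if the unrounded 24.5 is inflated), and 30 covers a loss of only 16.7%. With 25% lost, the unadjusted comparison at d = 0.8 has 75.6% to 77.4% power by the normal approximation or 73.6% to 75.6% by t test, compared with 80.7% and 79.2% if 25 per arm remained. The stated 80% is not delivered, by a modest margin.

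This rests on the protocol's own inputs, equal arms and, as its formula assumes, independent students. Allocating one school to each arm is a separate and larger matter that this correction does not address.

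**What to change.** Replace the attrition sentence in section 2.5 with one in which the numbers agree and the method is named. For example: *Thirty students per arm leave at least 25 evaluable if attrition is at most 16.7%, giving 79% power for d = 0.8 (two-sided 5% t test; 81% by the normal approximation). At 25% attrition 22 to 23 remain and power is 74% to 76% (76% to 77% by the normal approximation).*

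The cost is one sentence and a slightly less favourable power statement. Enrolment, design and analysis stay as they are. If the sponsor expects to gain power from the baseline adjustment, the assumed correlation should be stated and used in the calculation.

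Keeping 25% attrition and 80% power together would instead mean 34 per arm, 102 in total. That would also alter the peer-education arm, which section 2.4.2 builds from three subgroups of ten, so it is more than a change of wording. The correction does not depend on it.

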### Recruitment and randomization

2.6

Three high population public secondary high schools in both districts in Sari city will be selected purposefully. In each school, all 11th‐grade students will fill out the socio‐demographic menstrual characteristics checklist, GHQ‐28 Items, and PSST which is a retrospective questionnaire to screen eligible participants. After that, schools will be randomly allocated to one of three study arms: (a) Peer‐group education (IG1); (b) Health practitioner education (IG2); (c) Comparison Group (CG) by using a random number table. Following recruitment and verification of study eligibility, required sample size (30 students in each group) will be selected randomly by a random allocation sequence generating using the built‐in random number generator in Microsoft Excel (Cheusheva, 2020). They will complete the DRSP (during two consecutive menstrual cycles). Before random sampling, ten volunteer students will be selected as peer educators purposefully and will be trained by the PI. At the end of the final session, the PI will select six students as peer educators by assistance of school staff. Since the intervention is educational, it will not be possible to design a blind study. The students who meet the inclusion criteria will be informed completely about the protocol of the study.

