### Study design

2.2

This study is a three‐armed parallel‐group non‐masked clinical trial, with two intervention groups named intervention group 1 (IG1), intervention group2 (IG2) and comparison group (CG). For prevention of contamination bias, school allocation to different arms will be random. Also, selection of students from the total eligible students in each school for participation in IGs and CG will be random. Outcomes assessment in IGs will occur at baseline (T0) and at the end of intervention as well as its equivalent in the comparison group (T1). After baseline assessment, the participants will be informed of which group they are assigned to.

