### Intervention

2.4

In this study, the following steps will be implemented (Figure 1):

Schools will be purposefully selected from total schools in urban districts in Sari city;In each school, inclusion criteria will be assessed, including screening for moderate and severe PMS by PSST;After baseline assessment schools will be, randomly, allocated to one of three study arms: (a) Peer‐group education (IG1); (b) Health practitioner education (IG2); (c) comparison group (CG)All participants will be instructed to fill out the DRSP for two consecutive menstrual cycles;Re‐evaluation of exclusion criteria;Volunteer eligible students will be purposefully selected as peer educators and educated by the principal investigator (PI);The required sample for receiving interventions or participate as CG will be based on the random selection from the total eligible students in each school;Trained peer educators will implement the intervention in IG1;At the same time, the health practitioner will implement the intervention in IG2.

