### Statistical analysis

2.10

All analyses of the outcomes will performed as intention‐to‐treat analyses and following the TREND checklist. The normality of distribution will be examined by the Kolmogorov–Smirnov test. All quantitative variables will be expressed as mean ± *SD*. Categorical variables will be presented as frequencies and percentages. The chi‐square test will be used to test for differences between categorical variables. Baseline means differences will be tested using a one‐way analysis of variance (ANOVA or the non‐parametric equivalent of that Kruskal–Wallis). Analysis of covariance (ANCOVA) will be used to identify differences between the three groups at the end of the study, adjusting for baseline values and covariates. The comparison of mean values will be conducted within groups after the intervention period using paired sample *t* tests. *p* < .05 will be considered statistically significant. Statistical tests of the outcome measures will be performed using Statistical Package for the Social Sciences (SPSS version 18.0).

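### One school per arm: the education effect cannot be separated from the school effect, so the student-level p-values and the 80% power claim are not valid

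*Protocol article*

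**What the plan says.** Section 2.6 of the protocol article sets the number of schools: "Three high population public secondary high schools in both districts in Sari city will be selected purposefully". After screening, "schools will be randomly allocated to one of three study arms". Section 2.2 gives the reason: "For prevention of contamination bias, school allocation to different arms will be random".

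There is a second random step, at student level. Section 2.6 says the "required sample size (30 students in each group) will be selected randomly", and section 2.4 describes the same step as "random selection from the total eligible students in each school". It determines who enters the study from a school whose arm is already set. It does not assign students to arms.

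Section 2.5 computes the sample size for two independent groups: "Sample size will be determined at CI: 95% and Power: 80%, Large Cohen effect size = 0.8". The result is 25 per group, raised to 30 for attrition, with no ICC, design effect or number of schools. Section 2.10 plans the main comparison: "Analysis of covariance (ANCOVA) will be used to identify differences between the three groups at the end of the study", adjusted for baseline values and covariates, with significance at p < .05. No school term is named.

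**The concern.** The school is the unit that is randomised, and each arm holds one school. Anything that differs between the schools therefore also differs between the arms. Section 2.4.4 gives one example: every school has its own counsellor, who provides the routine education and answers menstrual questions. District is another, because three schools drawn from two districts leave one arm alone in its district.

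Both hypotheses in section 1.1 (peer education similar to practitioner education, and both better than comparison) rest on contrasts between arms. A significant contrast could be wholly a school difference, and a school difference could equally hide a real effect. The Discussion looks ahead to wide use of peer educators by schools, and that conclusion would rest on these contrasts.

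**Working it through.** **Inputs.** From the article: 3 schools, 3 arms, 30 students per arm (25 before the attrition allowance), two-sided 5%, 80% power, standardised difference 0.8. Assumed: ICC ρ of the baseline-adjusted outcome = 0.01, 0.02, 0.05, 0.10, because the article gives none.

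**1. The plan's own figure.** 2 × (1.96 + 0.84)² / 0.8² = 2 × 7.84 / 0.64 = 24.5, rounded up to 25. This matches section 2.5. Power at 25 per arm is 80.7% (normal approximation) or 79.1% (t test), but only if ρ = 0.

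**2. Degrees of freedom at the level of allocation.** Schools minus arms = 3 − 3 = 0. No standard error for the arm effect can be estimated at that level, whether by mixed model, cluster-robust variance or school means. This step needs no assumed ICC.

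**3. Error rate of the student-level test.** With n students per school and outcome variance σ²:

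- True variance of a difference between two arms: 2σ²[ρ + (1 − ρ)/n].
- Variance the ANCOVA assumes: 2σ²(1 − ρ)/n.
- Ratio: R = 1 + nρ/(1 − ρ). For n = 30 and ρ = 0.05, R = 1 + 1.5/0.95 = 2.58.
- True pairwise type I error: P(|t| > t₀.₉₇₅/√R) with 2n − 2 df. The three-group test is scaled by R in the same way, with 2 and 3(n − 1) df.
- Effective n per arm: n / [1 + (n − 1)ρ].

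| ρ | R (n = 30) | Pairwise type I, n = 30 | Three-group F, n = 30 | Effective n per arm (of 30) | Pairwise type I, n = 25 | Three-group F, n = 25 |
|---|---|---|---|---|---|---|
| 0.01 | 1.30 | 8.5% | 10% | 23 | 7.9% | 9% |
| 0.02 | 1.61 | 12.0% | 15% | 19 | 10.8% | 13% |
| 0.05 | 2.58 | 21.8% | 31% | 12 | 19.3% | 27% |
| 0.10 | 4.33 | 34.0% | 49% | 8 | 30.6% | 44% |

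A simulation of the three-group ANCOVA with a baseline covariate and 25 students per school (10,000 runs) agrees. It rejected a true null in 12.8%, 25.9% and 44.4% of runs at ρ = 0.02, 0.05 and 0.10.

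**4. Precision.** At ρ = 0.05 and n = 30 the design effect is 1 + 29 × 0.05 = 2.45. The 95% half-width is 1.96 × √(2 × 2.45/30) = 0.79 SD. The student-level analysis would show 1.96 × √(2 × 0.95/30) = 0.49 SD. The interval that allows for clustering is 1.6 times as wide, and its half-width is about the 0.8 SD the trial is planned on.

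**5. Power.** Even if ρ were known exactly, power at 0.8 SD with 25 per arm would be 72%, 64%, 48% and 34% across the four values. With 30 per arm it would be 78%, 69%, 51% and 35%. More students per school cannot solve this, since the variance of a difference never falls below 2ρσ².

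**The case against.** Several points can be made for the plan.

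- **Number of schools.** The sentence in 2.6 could mean three schools in each district, so six in all and two per arm. Arm and school would then not coincide completely. This is the less natural reading. Under it, ignoring clustering with 15 students per school still gives a pairwise type I error of about 7% to 22% over the same ICC range. A school-level pairwise t test with 2 df would have about 37% down to 22% power.
- **Baseline adjustment.** The ANCOVA adjusts for baseline and covariates, and the students are alike in grade, city, school type and PMS severity. Adjustment can therefore remove part of the measured intake differences. It does not remove school-specific change over time or unmeasured factors. A residual ICC of only 0.01 to 0.02 still gives 8.5% to 12%.
- **Number analysed.** The plan is powered on 25, not 30. The table shows both. The intention-to-treat wording makes 30 a fair base, and using 25 lowers the figures only modestly.
- **Contamination.** Preventing it is a sound reason to allocate schools. It is not a reason to have only one school per arm.
- **Wording.** The title calls this a non-masked clinical trial, not a randomised one. Sections 2.2 and 2.6 do claim random allocation of schools, so the limitation still has to be stated.
- **Feasibility.** The trial had launched and was recruiting, so adding schools may no longer be practical. This affects the choice of remedy, not the finding.

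**Conclusion.** The concern holds. On the plain reading there is one school per arm and 0 between-school degrees of freedom. An analysis plan that is not shown could not repair this, because the limit lies in the design. The nominal 5% error rate and the 80% power in section 2.5 require an ICC of zero.

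How far they are off rests on the assumed ICC range of 0.01 to 0.10, so the percentages are illustrative: with 30 students per school, about 8.5% to 34% pairwise and 10% to 49% for the three-group test. Neither hypothesis can be answered causally as the study is set up. Because the defect affects the primary comparison, it must be fixed.

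**What to change.** **Minimum, with the three schools kept.**

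- In 2.6, state the total number of schools without ambiguity.
- In 2.2, 2.5 and 2.10, state that arm coincides with school and that the study compares three schools rather than giving a randomised test of education type.
- In 2.5, withdraw the 80% power claim.
- In 2.10, report the ANCOVA differences with intervals widened for a stated ICC range, for example 0.01 to 0.10, and say that the ICC is assumed and not estimated from the trial.

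This costs protocol wording and one sensitivity analysis.

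**Preferred, only if the schools are not yet fixed.** Spread the same 90 students over several schools per arm, for example 3 schools × 10 students (which fits the IG1 subgroups of ten) or 5 × 6 (which does not). Randomise schools within district as far as the numbers allow, and analyse with a random school effect and small-sample degrees of freedom.

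Power must then be restated. At ICC 0.05 and a difference of 0.8 SD (df pooled over three arms / pairwise df):

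| Design per arm | 30 analysed | 25 analysed |
|---|---|---|
| 3 × 10 | 0.58 / 0.50 | 0.53 / 0.45 |
| 5 × 6 | 0.72 / 0.68 | 0.66 / 0.62 |

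Neither design reaches 80%. With 10 analysed students per school and pairwise df, 80% needs 4, 5, 5 or 6 schools per arm at ICC 0.01, 0.02, 0.05 or 0.10.

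The 90-student options need no more students, but they do need more school permissions and logistics, and peer-educator selection and training in each IG1 school. After launch that cost is substantial.

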### Informed consent

2.7

School principals will provide informed consent on behalf of their school to participate in the study and will be introduced PI to school staff to collaborate with her. The PI will obtain written informed consent from each 11th‐grade student and their parents /guardians. Consent can be withdrawn at any time, without affects the student's relationship with the school staff and research team.

### Outcomes

2.8

The primary outcome will be changes in PMS severity score between three groups over time that will be measured by DRSP. Secondary outcomes include changes in Premenstrual Dysphoric Disorder (by DRSP) and the General Health (by GHQ‐28 Items).

### Data collection and outcome measurement

2.9

#### Socio‐demographic‐menstrual characteristics checklist

2.9.1

The socio‐demographic‐menstrual characteristics checklist will fill out by the participants, which include following variables: Age, Marital status, Residential area (city/village), Parents’ education, Parents’ employment status, Height, Weight, Physical activity, Menarche age, Menstrual duration, Menstrual interval, Dysmenorrhea, Menstrual regularity and Familial history of PMS.

#### Premenstrual symptoms screening tool (PSST)

2.9.2

The PSST was developed by Steiner et al. in 2003. It is a retrospective screening tool to identify women who suffer from severe PMS. This tool has 19 items in two parts, the first part measures 14 symptoms, including mood, physical and behavioural symptoms of PMS, and the second part (the last 5 items) measures the effect of these symptoms on a person's life. For each item, four possible responses (never, mild, moderate and severe) are considered from zero to three. The reliability of the PSST as measured by Cronbach's alpha coefficient is reported 0.93, and its content validity ratio and content validity index are reported 0.7 and 0.8, respectively (Hariri et al., 2013; Steiner et al., 2003, 2011).

